### Study population

We aim to enroll 68 individuals with a biopsy-proven diagnosis of IBD, aged 18 years or older, who meet criteria for impaired IBD-related quality of life and report recent abdominal pain or bowel symptoms (Table 2). Impaired IBD-related quality of life will be reflected by a Short IBD questionnaire (SIBDQ) score < 60. We have chosen inclusion/exclusion criteria to permit as many people with symptomatic IBD as possible to participate safely, while maximizing generalizability of findings (Table 2). For example, prescribed hypnotics, over-the-counter sleep aids, and antidepressants will be permitted as their use is common in IBD, but these permitted medications will need to be stable for 30 days before and during the study. Changes in medications to treat IBD during follow-up will be permitted as this is typical in clinical practice (although changes in corticosteroids will be cause for exclusion due to impact on sleep quality which could confound study results, see Table 2). Participants will be able to continue psychological therapy, physical therapy, and exercise if the treatment was started 30 days prior to enrollment and continues during the study period. Participants must be physically able to travel for the study visits and have no experience with light treatment in the past year. Participation will be scheduled ≥ 1 month from night work, travel outside the eastern time zone, other research participation, and will be scheduled during a period with minimal special events (e.g., weddings, concerts, exams).

**Table 2 Tab2:** Inclusion and exclusion criteria

Inclusion criteria
1. Age ≥ 18 years old
2. Biopsy-proven IBD
3. Impaired quality of life: Short IBD Questionnaire (SIBDQ) < 60
4. Symptoms: at least “some of the time” abdominal pain or bowel symptoms on SIBDQ
5. Fluent in English
6. Physically able to travel to study visits, within 1.5 h drive of study location

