### Statistical power and analysis

We plan to enroll 68 individuals with a biopsy-proven diagnosis of IBD, aged 18 years or older, who meet criteria for impaired IBD-related quality of life and report recent abdominal pain or bowel symptoms, with the aim of a final sample of 50 study participants, assuming 25% attrition during the 5-week study period. A 9-point change in SIBDQ score is considered clinically meaningful and corresponds to a standardized effect size of 1.0 SD [35, 58, 59]. This proposed sample of 50 participants (25 participants in the morning light treatment group and 25 participants in the TAU group) provides ≥ 80% power to detect a clinically meaningful change in our primary outcome measure (SIBDQ) with a two-tailed alpha of 0.05.

We will conduct an intention-to-treat and completer analyses. We will report descriptive statistics of the data by each assessment time (pre-treatment, post-treatment) using appropriate summary statistics. We will analyze both primary and secondary outcomes using a mixed-effects longitudinal data model with participants as random intercepts to account for between participant variability. Predictors will include a post-randomization time indicator, intervention group indicator, and the interaction of time by group. We will examine the extent and pattern of key missing outcomes data and if missingness is greater than 15%, we will assess for baseline characteristics predictive of missingness post-randomization and will include those baseline characteristics as covariates in the final model. While clinician-rated disease activity will be examined as a continuous variable, we will also examine the proportion of participants who show clinical response and/or clinical remission as a binary variable using a generalized linear mixed model with logit link. Clinical response is defined as a decrease in SCCAI score ≥ 3 or a decrease in HBI score ≥ 3. Clinical remission is defined as an SCCAI score of ≤ 2 or an HBI score of < 5.^40,41^

We will explore steroid use, severity of RLS, and biological sex as potential moderators of any treatment effects. We will also perform subgroup analyses to explore differences in responses to morning light treatment between participants with CD versus UC/IBD-unclassified to inform future studies.

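### Clinical response has one value per participant, so the logit mixed model named for it is not identified, and with no HBI or SCCAI minimum at entry some participants cannot respond

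*Protocol article*

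**What the plan says.** All of this is in the protocol article.

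- **Response** (Statistical power and analysis) is a change between two visits: "Clinical response is defined as a decrease in SCCAI score ≥ 3 or a decrease in HBI score ≥ 3".
- **Remission** (same section) is a state at a single visit, met at an SCCAI of 2 or less or an HBI below 5.
- **Model** (same section): the binary analysis covers "the proportion of participants who show clinical response and/or clinical remission as a binary variable using a generalized linear mixed model"; the link is logit. The sentence does not restate its random effects. The only ones the section names belong to the general model, a "mixed-effects longitudinal data model with participants as random intercepts to account for between participant variability", with time, group and their interaction as predictors.
- **Timing** (Outcome measures; Table 3): HBI and SCCAI are scored at visits 3 and 7 only. Visit 3 is also the randomisation visit.
- **Eligibility** (Table 2): entry rests on the SIBDQ, through a total below 60 ("Impaired quality of life: Short IBD Questionnaire (SIBDQ") and a symptom item ("abdominal pain or bowel symptoms on SIBDQ"). Neither the inclusion nor the exclusion list sets a minimum HBI or SCCAI.
- **Denominator**: the section does not limit response to participants able to fall by 3 points, or remission to participants not yet in remission.

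**The concern.** There are two separate problems.

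**Model.** A random intercept needs repeated values within a participant. Response compares visit 7 with visit 3, so it exists once per participant. Combining response with remission in one indicator, which the and/or wording permits, carries the same problem into the composite.

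**Who can meet the endpoint.** The SIBDQ is a quality-of-life questionnaire, whereas HBI and SCCAI are clinician-rated indices first scored at visit 3. Passing the SIBDQ criteria does not guarantee an index score high enough to fall by 3. A low scorer is a certain non-responder under either treatment. The same participant is in remission before treatment starts and can still be counted in remission after worsening, for example from HBI 1 to HBI 4.

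Clinician-rated disease activity is a stated secondary objective, and the trial is meant to inform a larger confirmatory one. Response and remission proportions are figures that a later trial could plan from.

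**Working it through.** **The plan's own figure.** The only design calculation concerns the primary outcome: 25 per arm, a difference of 1.0 SD, two-sided alpha 0.05. The normal approximation gives Φ(√(25/2) × 1.0 − 1.96) = Φ(1.576) = 94.2%, and the noncentral t gives 93.4%. Both agree with the stated 80% or more. The plan gives no figure for the binary endpoints.

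**Step 1. Visit 3 score against the two definitions.**

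| Visit 3 score | Fall of 3 possible? | Already in remission? |
|---|---|---|
| HBI 0–2 | No | Yes |
| HBI 3–4 | Yes | Yes |
| HBI 5 or more | Yes | No |
| SCCAI 0–2 | No | Yes |
| SCCAI 3 or more | Yes | No |

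Being unable to respond and being in remission coincide for SCCAI. For HBI they differ at 3 and 4.

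**Step 2. Random intercept with one value per participant.** The marginal probability of response in an arm is π = ∫ expit(α + β·arm + σz) φ(z) dz. For any σ, α and β can be chosen to reproduce the two observed proportions, so the likelihood is flat in σ. Take illustrative counts (assumed, not from the document) of 11/25 and 5/25:

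- Maximum log-likelihood = 11 ln 0.44 + 14 ln 0.56 + 5 ln 0.20 + 20 ln 0.80 = −29.658.
- With σ = 0, the odds ratio is (0.44/0.56)/(0.20/0.80) = 3.14.

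| σ | Log-likelihood | Odds ratio |
|---|---|---|
| 0 | −29.658 | 3.14 |
| 1 | −29.658 | 3.89 |
| 2 | −29.658 | 6.24 |
| 4 | −29.658 | 20.59 |

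The data cannot choose between these rows.

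**Step 3. Coding response as 0 for everyone at visit 3.** This would supply a second row per participant and allow a time term. With the same counts and σ = 1, moving the baseline intercept through −2, −4, −6, −8, −12 and −16 raises the log-likelihood through −38.11, −31.08, −29.86, −29.69, −29.659 and −29.658. The time coefficient meanwhile grows from 0.5 to 14.4. This is complete separation on time, with no finite estimate.

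**Step 4. Effect of participants unable to respond.** Assume response of 60% versus 25% among those able to respond, a share f unable to, 25 per arm and a pooled z-test at two-sided 0.05. In everyone, the rates are 0.60(1 − f) and 0.25(1 − f). After restriction, the rates stay at 0.60 and 0.25, and each arm's size is binomial(25, 1 − f).

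| f | Rates in everyone | Difference (points) | Power, everyone | Power, restricted |
|---|---|---|---|---|
| 20% | 48% vs 20% | 28 | 58% | 63% |
| 40% | 36% vs 15% | 21 | 42% | 51% |
| 50% | 30% vs 12.5% | 17.5 | 34% | 44% |

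The gain from restriction is 5, 9 and 10 points. The document gives neither f nor the response rates.

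**The case against.** **Scope.** This is a condensed article whose analysis plan is not shown, and denominators and model details are often left to that plan. Leaving out the denominator would not be a finding by itself. But the article does state the definition, the visits and the model class, and for response these do not fit together.

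**Fitting.** A reader might infer that the software will fail. It may instead return a variance near zero, which amounts to ordinary logistic regression. The supported statement is that the model is not identified. Complete separation arises only if visit 3 is coded 0 for everyone, which the article does not say.

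**Remission.** A reader might infer that the model is also wrong for remission, or that remissions present at entry are credited to treatment. The document does not support this. Remission is a state scorable at both visits, so a mixed model with time, group and their interaction can be fitted and carries entry status. Randomisation also gives both arms the same expected share at entry. For example, assume 40% in remission at entry, 85% of them staying so in both arms, and new remission of 60% versus 25% in the rest. Visit 7 remission is then 0.36 + 0.34 = 70% versus 0.15 + 0.34 = 49%. The carried-over 34 points are about half of the light-arm figure and most of the control figure, but they cancel from the 21-point difference. What stands is that raw visit 7 percentages need entry status beside them.

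**Remission is not inability to respond.** A participant with HBI 3 or 4 is in remission yet can still fall by 3, so treating everyone in remission as unable to respond would overstate the dilution in Crohn's disease.

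**Power.** It is tempting to set the diluted power against the 76% obtained when all 25 per arm can respond. No analysis can restore that, because most of the loss comes from having fewer participants able to change.

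**Importance.** The symptom criterion makes very low scores less likely, though it does not exclude them. The binary summaries supplement a continuous analysis in a trial described as preliminary.

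**Conclusion.** The point holds for clinical response and for any composite containing it. One value per participant identifies neither the random-intercept variance nor the conditional odds ratio. This follows from the definition and the visit schedule and needs no assumed rates; the 3.14 to 20.59 range only illustrates it. It does assume that the binary model carries the participant intercept, the only random effect the section names.

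It also follows from the definitions that participants scoring 0 to 2 at visit 3 cannot respond, and that those with HBI below 5 or SCCAI of 2 or less already meet remission. How many would enter at those levels is unknown. Under the assumed 60% versus 25%, restricting the response analysis is worth about 5 to 10 points of power for 20% to 50% unable to respond, so the case rests mainly on interpretability.

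The plan should be changed here, but the matter is moderate. The primary SIBDQ analysis, its power statement and the continuous disease-activity analysis are untouched.

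**What to change.** 1. Report response and remission as separate endpoints.
2. Analyse response once, at visit 7, by logistic regression or a risk difference with arm, visit 3 score and disease type (Crohn's disease versus ulcerative colitis or IBD-unclassified), among participants whose visit 3 score is at least 3. This keeps HBI 3 and 4, who can respond.
3. Analyse remission at visit 7 among participants not in remission at visit 3, or in everyone with visit 3 remission status in the model. The mixed model with a time-by-group term is also acceptable for remission. Report alongside it the proportion of those in remission at visit 3 who remain so.
4. Keep the continuous analysis in all participants.

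The cost is a change of analysis wording and a smaller denominator for these supplementary binary summaries. Visit 3 scores are pre-treatment measurements, so restricting or adjusting on them introduces no post-randomisation selection. Giving up the mixed model for response loses no participant, because someone without a visit 7 score has no response value under either method.

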## Discussion

This protocol manuscript describes a single center randomized controlled trial of morning light treatment vs. TAU in IBD. This study will provide insight into the effect of morning light treatment on IBD-related quality of life, depression, sleep quality, and clinical disease activity for patients with IBD to inform its role as an adjunctive therapy for patients with active symptoms. Despite the availability of effective IBD-targeted pharmacological therapies, many patients with IBD continue to suffer from inadequate disease control and impaired health-related quality of life. Many patients also identify preferences for non-pharmacological treatment options, but few evidence-based non-pharmacologic strategies exist for IBD. Therefore, morning light treatment has the potential to play an important role in IBD treatment if found to be efficacious. Based on published literature and our prior work in chronic pain populations, morning light treatment has the potential to improve not only mood and sleep in IBD, but also improve gastrointestinal symptoms and possibly even intestinal inflammation. Even if morning light treatment were to only improve mood and sleep in patients with IBD, this treatment would assist at least 50% of IBD patients who suffer from such symptoms [4–8]. 

The strength of this study includes the randomized trial design and control group, blinding of study staff directly involved in assessing study outcomes, and a well-described conceptual model of the potential mechanistic relationship between morning light treatment and study outcomes. The anticipated study limitations include exclusion of patients with an ileostomy, colostomy, ileoanal pouch, ileorectal anastomosis, or short bowel syndroe which will limit generalizability of study findings to such patients who have undergone these major surgical procedures. Further, the study period is limited to five weeks and so long-term effects of morning light treatment in IBD will not be evaluated. However, we will plan to test the long-term effects of morning light treatment in IBD in future work.

This is the first NIH-funded randomized controlled trial of morning light treatment in IBD and has the potential to improve our understanding of the impact of morning light treatment on patients with IBD and fill a gap in adjunctive non-pharmacological IBD treatment. This study will also increase our understanding of the mechanistic relationships between sleep, mood, clinical disease activity, and IBD symptoms. If found to be efficacious, morning light treatment can be further examined in a larger clinical trial with the possibility of remote study visits to increase ease of participation to patients and a longer follow up period.

## Data Availability

No datasets were generated or analysed during the current study.

## Abbreviations

IBD: Inflammatory bowel disease
TAU: Treatment as usual
CD: Crohn’s disease
UC: Ulcerative colitis
PHQ-9: Patient Health Questionnaire
HBI: Harvey Bradshaw Index
SCCAI: Simple Clinical Colitis Activity Index
SIBDQ: Short Inflammatory Bowel Disease Questionnaire
CD-PRO: Crohn’s disease-patient reported outcomes
UC-PRO: Ulcerative colitis-patient reported outcomes
RLS: Restless leg syndrome
TIB: Time in bed
TST: Total sleep time
WASO: Wake after sleep onset
SE: Sleep efficiency
SAFTEE: Systematic Assessment for Treatment Emergent Events
